# STUDY POPULATION

## Population (base)

The research population will consist of 96 child-parents triads (total 288 participants). Parents of children aged 4 to 8 years are eligible for participating when their child is considered ‘overweight or obese’. The sample is expected to include relatively many children of low socio-economic status and ethnic minorities. This sample is drawn from medical reports of 2600 children in the Westelijke Mijnstreek and Eastern South Limburg, who are aged 4-8 years. Of these children, about 12.4% is overweight and 3.1% is obese, and 50% is expected to participate in the program. Therefore 9 months are planned to recruit parents of 96 4 to 8-year-old children

## Inclusion criteria

Parents are eligible for inclusion when: 1) their child is aged 4 to 8-years-old, and 2) when their child is labelled as overweight or obese after calculating the BMI and by using the international cut-off points of Cole et al. (15) (which are based on six large nationally representative cross sectional surveys on growth including the Netherlands). Parents who agree to participate in the study, and both sign for informed consent, are included in the study.

## Exclusion criteria

Children who have a medical cause for their overweight and children of parents who both do not speak the Dutch language are excluded from the current study.

## Sample size calculation

The expected difference between the intervention and control condition is 0.30 BMI-points over 6 months (based on Robinson (16)). This difference would imply and approximated relative weight loss of 1480 grams per year in the experimental condition (1020 grams weight gain versus 2500 grams weight gain in the control condition). Maintained behavioural changes would then lead a child in the experimental condition to a weight corresponding to the 50th percentile when it reaches the age of eight years.

The expected difference between both conditions would require a sample of 38 families in each condition to detect this difference with a power of .90 and p<.05. Adjusting for attrition, a total of 96 families will be randomly assigned to the intervention of control condition. Given an expected 10% of children to meet the inclusion criteria, 2600 4-year-olds that are aged 4-years old, and 50% participation-rate, recruitment is expected to take 9 months. Unless conflicting results from the pilot study, group sessions will consist of 8 families, resulting in 6 groups in the intervention condition.

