| **Randomization (on individual level) to one of the two conditions** | |
| **Intervention condition (N = 48)** | **Control condition (N = 48)** |
| 8 parental group training sessions (week 1-8)  **↓**  2 individual telephone sessions (week 9-10)  **↓**  1 parental group training sessions (week 11)  **↓**  2 individual telephone sessions (week 12-13)  **↓**  1 final parental group training session (week 14) | Parents receive a Time Machine, web-based tailored feedback about providing a good parental example for your child regarding diet and physical activity, and two leaflets: one about healthy nutrition and physical activity and one about positive parenting. |
| **Posttest measurements (immediately after the intervention, 14 weeks after baseline)** | |
| **Parents** | **Children** |
| Follow-up questionnaire, follow-up anthropometric measurements and Actigraph accelerometer | Follow-up anthropometric measurements (not deuterium dilution) and Actigraph accelerometer |
| **Posttest measurements (12 months after baseline)** | |
| **Parents** | **Children** |
| Follow-up questionnaire parents, follow-up anthropometric measurements and Actigraph accelerometer | Follow-up anthropometric measurements (including deuterium dilution) and Actigraph accelerometer |

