# METHODS

## Study parameters/endpoints

### Main study parameter/endpoint

The primary objective of this study is to test the effectiveness of the intervention in terms of preventing overweight and obese children from excessive weight gain. The main study parameter is children’s body composition, determined by BMI z-score (calculated by weight, height, age and gender), waist circumference, and fat mass (assessed via biceps and triceps skinfold and deuterium). BMI, waist circumference, and skinfold is measured at baseline, 14 weeks (directly following the intervention) and 12 months follow-up. Deuterium is measured only at baseline and 12 months follow-up.

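### The stated 90% power is for raw BMI over 6 months, which is not a planned primary comparison, and the 1480 g per year given for that effect does not follow from it

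*Protocol*

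**What the plan says.** The Sample size calculation section of the protocol starts from this effect: "The expected difference between the intervention and control condition is 0.30 BMI-points over 6 months". It translates the effect into body weight: "This difference would imply and approximated relative weight loss of 1480 grams per year in the experimental condition", with the arm figures given as "1020 grams weight gain versus 2500 grams weight gain in the control condition". It then says that behavioural change, if maintained, would bring an intervention child to the 50th weight percentile by age eight. The sample size statement is that the difference "would require a sample of 38 families in each condition to detect this difference with a power of .90 and p<.05". The step to the number randomised is "Adjusting for attrition, a total of 96 families will be randomly assigned". The section gives no SD, no sidedness and no attrition rate.

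The outcome sections describe different quantities. Under Main study parameter/endpoint, child body composition is "determined by BMI z-score (calculated by weight, height, age and gender), waist circumference, and fat mass". The primary objective names BMI z-score and fat mass, and the Statistical Analysis section lists the same two among the outcomes to be modelled. Raw child BMI is not listed there.

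The flow chart under Study Design has two post-baseline measurement points: one at 14 weeks, and "Posttest measurements (12 months after baseline"). The Main study parameter/endpoint and Study procedures sections give the same anthropometry schedule. The only mention of 6 months as a measurement time is a bullet in Study procedures that puts deuterium at baseline and 6 months. It conflicts with the Study Design text, the flow chart and the endpoint section, which all put the second deuterium measurement at 12 months.

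**The concern.** A power statement should describe a comparison that the trial will make. Here both the variable (raw BMI rather than BMI z-score, waist circumference or fat mass) and the time (6 months rather than 14 weeks or 12 months) differ from what is planned. The paragraph is the only justification for the number of families, so a reader cannot tell what power the trial has for its own primary measures.

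The second problem is internal. The effect is stated once in BMI-points and once in grams, and the text says that one implies the other. If they disagree, the reader does not know which is the design target, and the clinical-relevance argument (the 50th percentile by age eight) rests on the larger one.

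**Working it through.** **Inputs.** From the Sample size calculation section: difference 0.30 BMI-points over 6 months; 38 per condition; power 0.90; alpha 0.05; 96 randomised; yearly weight gains of 1020 g and 2500 g. From the flow chart: 48 per condition. Not in the documents, so assumed: a two-sided test, child height (1.00 to 1.40 m, with 1.50 m as a stress test), and a linear course of the effect beyond 6 months.

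**1. The plan's own 38.** It cannot be computed forwards because no SD is given. Backwards, with n = 2(z₀.₉₇₅ + z₀.₉₀)² / d² and n = 38:

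- d = (1.960 + 1.282) × √(2/38) = 0.744, so SD = 0.30 / 0.744 = 0.403.
- With the noncentral t distribution, d = 0.7535 and SD = 0.398.
- With a one-sided test, SD = 0.447 (0.443 with t).
- Forward check with SD 0.40: n = 2 × 3.2415² × (0.40/0.30)² = 37.4, rounded up to 38.

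So 38 is arithmetically possible with an unstated SD of about 0.40 BMI-points. The step from 76 to 96 families corresponds to 1 − 76/96 = 20.8% attrition.

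**2. Does that calculation match a planned comparison?**

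| | Sample size section | Outcome sections |
|---|---|---|
| Variable | raw BMI | BMI z-score, waist circumference, fat mass |
| Time | 6 months | 14 weeks and 12 months (deuterium at 12 months only, apart from the stray bullet) |

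Neither row matches. The documents give no expected difference and no SD for BMI z-score, waist circumference or fat mass, so power for those cannot be computed from them.

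**3. Grams against BMI-points.** The arm figures subtract correctly: 2500 − 1020 = 1480 g. With equal mean heights in the randomised arms, weight difference = BMI difference × height². If the effect continues linearly, it is 2 × 0.30 = 0.60 BMI-points at one year.

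| Assumed height | 0.60 BMI-points per year | 1480 g as a multiple | 740 g per 6 months in BMI-points |
|---|---|---|---|
| 1.00 m | 600 g | 2.5 | 0.74 |
| 1.10 m | 726 g | 2.0 | 0.61 |
| 1.20 m | 864 g | 1.7 | 0.51 |
| 1.30 m | 1014 g | 1.5 | 0.44 |
| 1.40 m | 1176 g | 1.3 | 0.38 |
| 1.50 m (stress test) | 1350 g | 1.1 | 0.33 |

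The two statements agree only at √(1.48/0.60) = 1.57 m. If the difference merely stays at 0.30 BMI-points to 12 months, it is 300 to 588 g over 1.00 to 1.40 m, and agreement would need √(1.48/0.30) = 2.22 m.

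**4. Sensitivity of power to the missing inputs.** For raw BMI, 38 per arm, two-sided t-test, with illustrative SDs that have no source in the documents:

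| Assumed SD | Effect stays at 0.30 | Effect continues to 0.60 at 12 months |
|---|---|---|
| 0.5 | 73% | 99.9% |
| 0.6 | 58% | 99.0% |
| 0.8 | 36% | 89.7% |

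The answer depends on the SD and on the course of the effect, and the protocol states neither.

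**The case against.** The strongest reply has four parts.

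- **BMI z-score is BMI rescaled for age and sex**, and the endpoint section also lists BMI among the measurements at 14 weeks and 12 months. The calculation is therefore for a closely related quantity. This stands as far as it goes: the power is untransferred, not irrelevant. It does not supply the z-score difference, its SD or the matching visit.
- **The figure 38 is reproducible** with an SD near 0.40. This stands. Nothing here shows that the number of families is wrong.
- **The gram figure is called approximate and serves as illustration.** Nothing shows that it entered the calculation, since 38 fits the 0.30 figure. This also stands, and it makes the gram error the lesser part. But a factor of 1.3 to 2.5 is more than rounding, and the percentile sentence is drawn from it.
- **Child height is not in the documents.** True. The disagreement nevertheless holds at every height below 1.57 m under the linear reading, and doubling the effect is the more favourable of the two readings considered.

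Two stronger conclusions are tempting. A reader might infer that the trial is underpowered, citing 36% to 73%. Those figures take an assumed SD range and only the maintained effect; the continuing effect at the same SDs gives about 90% or more. A reader might also infer that a null result would be uninterpretable. That does not follow, because a null result is read from its estimate and confidence interval, not from the planning calculation.

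**Conclusion.** The point holds in two parts and should be fixed.

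First, the 90% power is attached to raw BMI over 6 months and is not established for any planned primary comparison. This rests on the protocol's text alone. The size and direction of any change in power on the z-score scale are unknown.

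Second, 0.30 BMI-points over 6 months does not imply 1480 g per year. The overstatement is about 1.3 to 2.5 times at assumed heights of 1.00 to 1.40 m with linear continuation, and about 2.5 to 4.9 times (1480/588 to 1480/300) if the effect only stays at 0.30. The percentile sentence is therefore unsupported as written. It cannot be called false, because the protocol gives neither a starting weight nor a growth reference for it.

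The documents do not support saying that 38 per arm is an arithmetic error, or that the trial is underpowered.

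**What to change.** - Restate the sample size paragraph for a primary measure and a visit that the trial uses, for example BMI z-score at 12 months. Give the expected difference, its SD and source, and the sidedness of alpha. Report the power that 38 completers per arm (96 randomised) gives for that comparison, and state the attrition rate.
- If the 0.30 BMI-point effect is kept as the starting point, say whether it is expected to continue, hold or fade by 12 months, and show how it converts to the chosen measure.
- Replace the 1480 g figure by BMI difference × height², with the height stated. Recompute the 50th-percentile sentence from that, with its growth reference and starting weight, or delete it.
- Reconcile the 6-month deuterium entry in Study procedures with the Study Design text, the flow chart and the endpoint section.

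The cost is protocol wording and one recalculation. The restatement itself adds no families or visits. The power reported may turn out higher or lower than 90%.

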## Randomisation, blinding and treatment allocation

Block randomisation (n = 4) will be performed on the individual level. After parents of four families decide to participate in the study, they will be randomised to either the experimental condition or the control condition.

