## Data Safety Monitoring Board (DSMB)

# N.a.

# STATISTICAL ANALYSIS

Primary and secondary outcome parameters will be described via descriptive statistics. Quantitative continuous variables will be presented by use of means and standard deviations. Of categorical data, percentages will be presented of respondents falling in each of the possible categories.

Both univariate and multivariate multilevel analyses (correcting for group effects) are conducted to determine the effect of the intervention on (changes in) BMI z-score, fat mass, children’s lifestyle (screen-viewing behaviour, snacking behaviour, soft-drink consumption, fruit-and vegetable consumption, and physical activity level), parenting self-efficacy, parental skills, parental BMI, parental fat mass, and parental physical activity level. In the multilevel analyses, relevant confounders such as the child’s age, gender, ethnicity and parental socio-economic status.

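### The 90% power figure makes no allowance for the intervention-group effect that the planned analysis corrects for

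*Protocol*

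**What the plan says.** The Sample size calculation section of the protocol starts from an effect: "The expected difference between the intervention and control condition is 0.30 BMI-points over 6 months". It then says that this "would require a sample of 38 families in each condition to detect this difference with a power of .90 and p<.05". The only step from there to the randomised total is for drop-out: "Adjusting for attrition, a total of 96 families will be randomly assigned". The section gives no SD, sidedness, attrition rate, ICC or design effect.

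The same section sets out how the intervention is delivered, subject to the pilot results: "group sessions will consist of 8 families, resulting in 6 groups in the intervention condition". The Intervention section confirms groups formed by the parents of eight children. Control families receive leaflets, web-based feedback and a screen-time device, and so belong to no group. Allocation is by family: "Block randomisation (n = 4) will be performed on the individual level".

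The Statistical analysis section plans "multilevel analyses (correcting for group effects" for BMI z-score, fat mass and the secondary outcomes.

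**The concern.** Families trained together share a trainer and sessions built on joint practice, so their outcomes may be correlated. The protocol accepts this in its analysis section, where the group effect is to be corrected for, but the sample size section leaves it out. The two sections therefore describe different analyses: the power figure belongs to a comparison of independent families, while the planned model carries a group effect in one arm.

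What is at stake is how the primary result is read. A null finding would be judged against a claimed 90% chance of detecting the expected difference, and the planned analysis has a smaller chance than that if outcomes correlate within groups at all.

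**Working it through.** **Inputs from the protocol.** Difference 0.30 BMI points; 38 evaluable families per arm; power .90; p<.05; 48 randomised per arm; 6 intervention groups of 8; ungrouped controls.

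**Assumptions.** Two-sided test; SD back-solved; ICC from 0 to .10, because the protocol gives none.

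**Step 1: reproduce the plan's figure.** Without an SD, 38 cannot be derived directly. Solving the two-sample formula for the SD gives

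SD = 0.30 / [(1.960 + 1.282) × √(2/38)] = 0.403 (0.398 from a t test; 0.447 if one-sided).

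The round value 0.40, two-sided, gives n = 2 × (3.2415)² × 0.40² / 0.30² = 37.4, so 38 per arm. Attrition of 20% then gives 38/0.80 = 47.5, so 48 per arm and 96 in total. Both of the plan's figures are reproduced with independent families and nothing left over for grouping. The attrition implied by 38 out of 48 is 20.8%.

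**Step 2: allow for grouping in the intervention arm only.** With m evaluable families per group, the design effect is DE = 1 + (m − 1) × ICC, and

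SE² = SD² × (DE + 1) / n.

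At n = 38 per arm, m = 38/6 = 6.33. The back-solved SD makes the ratio of difference to standard error 3.2415 under independence, so

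power = Φ(3.2415 / √[(1 + DE)/2] − 1.960).

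Example at ICC .05: DE = 1 + 5.33 × .05 = 1.267; 3.2415/√1.133 = 3.045; Φ(1.085) = 86.1%.

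**Step 3: allow for having only six groups.** If the variance of the intervention mean is estimated from six group means, the Satterthwaite degrees of freedom at 38 per arm are (DE + 1)² / (DE²/5 + 1/37), and power comes from the noncentral t. At ICC .05 this gives 14.8 degrees of freedom.

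| ICC | 38/arm: DE | 38/arm: normal | 38/arm: six-group df | 48/arm: DE | 48/arm: normal | 48/arm: six-group df |
|---|---|---|---|---|---|---|
| 0 | 1.00 | 90.0% | 86.4% | 1.00 | 95.4% | 93.1% |
| .01 | 1.05 | 89.2% | 85.4% | 1.07 | 94.7% | 92.1% |
| .02 | 1.11 | 88.5% | 84.3% | 1.14 | 94.1% | 91.1% |
| .05 | 1.27 | 86.1% | 81.1% | 1.35 | 91.9% | 87.9% |
| .10 | 1.53 | 82.1% | 75.8% | 1.70 | 88.0% | 82.1% |

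The 48-per-arm columns use m = 8 and assume that no family is lost.

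**Step 4: separate the two sources of loss.** The ICC 0 row shows that the small degrees of freedom alone cost 90.0 − 86.4 = 3.6 points at 38 per arm. The loss from correlation itself is therefore best read down a column: 0.8, 1.5, 3.9 and 7.9 points on the normal approximation at ICC .01, .02, .05 and .10.

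**Step 5: sensitivity to sidedness.** If 38 came from a one-sided test, the ratio under independence is 1.645 + 1.282 = 2.926. Power is then Φ(2.926/√1.133 − 1.645) = 87% at ICC .05 and Φ(2.926/√1.267 − 1.645) = 83% at ICC .10. The picture does not change.

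**The case against.** The strongest reply is that the amount is not known. The ICC is not in the protocol, and at .01 the normal-approximation loss is under one point. That stands: the direction is certain for any positive ICC, but the size is not. The SD is likewise inferred from the plan's own 38, so independence is a strong inference and not something the protocol states.

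A second reply is that 96 families give slack. If all 48 per arm were retained, normal-approximation power would stay at or above 90% up to an ICC of about .075; with six-group degrees of freedom it would still be 90.1% at ICC .03. This is true, but the protocol has already assigned those families to attrition and cannot count them twice. If attrition turns out well below the implied 20.8%, part of the margin would become real.

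A third reply is that analysing change and adjusting for covariates such as age and gender, as planned, may cut residual variance and recover some power. That is possible, but the protocol does not quantify it or use it in the calculation.

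Two stronger readings are tempting, and the document supports neither. A reader might infer that the multilevel model will impose the same group structure on both arms. The Statistical analysis section specifies no such model, and its wording is compatible with a group effect in the intervention arm only. A reader might also infer that both parents' values will be analysed as independent records. The section does not say so; one parent, a couple mean or a family level would all fit. Random-effect structure and degrees-of-freedom method are commonly left to the statistical analysis plan, so their absence here is no error.

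**Conclusion.** The point holds in a narrow form. The stated power of .90 belongs to a comparison of independent families, while the analysis the protocol commits to corrects for a group effect that the sample size ignores. At 38 evaluable families per arm, power is below 90% for any positive ICC.

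Across ICC .01 to .10 it runs from about 89% down to 82% on the normal approximation, and from about 85% down to 76% with six-group degrees of freedom. These figures assume a two-sided test, an SD of about 0.40 back-solved from the plan, equal group sizes and clustering in the intervention arm only. Applying a design effect to both arms would overstate the loss.

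The documents do not support saying that the trial is badly underpowered. The shortfall runs from negligible to material, depending on an ICC that nobody has stated. The statement should be corrected, but the point does not undermine the design.

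**What to change.** In the Sample size calculation section:

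- State the SD, the sidedness of the test and the attrition rate behind the step from 38 to 48 per arm.
- State an assumed ICC range for the training groups, for example .01 to .10.
- Restate power at the planned 96 families, after the stated attrition, with grouping in the intervention arm only and control families treated as ungrouped. Say whether the figure allows for having only six groups.

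This is a change of wording and calculation. It needs no extra families and no change to randomisation or delivery. The cost is a stated power somewhat below 90%, which is the more honest figure against which to read a null result.

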# TREATMENT OF SUBJECTS

## Intervention

Forty-eight parent pairs who are assigned to the intervention condition will receive a 14-week intervention which consists of eight 120-minute parental group training sessions, two 15-30-minute individual telephone session for parents, one 120-minute parental group training session, another two 15-30-minute individual telephone session for parents and a final 120-minute group training session.

The health educators who provide training to the parents have followed an official 3-day Triple P level 4 training by the Dutch Youth Institute (Nederlandse Jeugd Instituut) and received accreditation for this training. In addition, before the start of the intervention, the health educators will be dedicated to childhood overweight-related topics.

The group size for the group sessions will be formed by the parents of eight children. The methodology will follow the principles of Lifestyle Triple P, an intervention which was originally developed and tested at the Queensland University in Australia. A yet unpublished RCT showed that Lifestyle Triple P resulted in increased parenting self-efficacy, reduced effective parenting and decreased children’s BMI and body fat (13). Lifestyle Triple P consists of the Triple P intervention, which is used worldwide to manage behavioural problems among children (17), with additional sessions focusing on environmental influences on energy balance-related behaviours in children. Active skills training methods are employed to help parents acquire new knowledge and skills: e.g. brief presentations alternated with group discussion, video and live demonstrations of parenting skills, rehearsal of skills using role plays and peer modeling, and small group problem solving exercises. Between sessions, parents complete homework tasks in order to apply new knowledge and skills in their own home situation. Each family is provided with a parent workbook that contains all the information and activities presented in the sessions. An overview of the topics and strategies is provided in figure 1.

Figure 1: Overview of the topics and strategies per session

| **Session** | **Topics** | **Strategies** |
| --- | --- | --- |
| Session 1: Preparing for change | Nature and causes of obesity  Overview of Lifestyle Triple P  Readiness to change |  |
| Session 2: Understanding nutrition | Increasing children’s self esteem  Food groups and daily severs  Nutrition goals | Spend quality time with your child  Talk to your child  Show affection |
| Session 3: Understanding physical activity | Encouraging healthy behaviours  Physical activity goals  Increasing incidental activity  Reducing sugar intake | Give frequent praise  Set a good example  Replace foods high in added sugar  Provide water as a regular drink  Make family leisure time active  Encourage active transport |
| Session 4: Using rewards and modifying recipes | Using behaviour charts  Reducing fat intake  Modifying recipes | Use behaviour charts  Buy low fat foods  Use low fat cooking methods  Replace high fat ingredients |
| Session 5: Limiting sedentary activity and reading food labels | Limiting sedentary activities  Establishing ground rules  Reading food labels | Establish clear ground rules  Use directed discussion to deal with rule-breaking  Read food labels  Limit sedentary activities |
| Session 6: Playing active games | Providing active alternatives  Increasing movement skills | Provide active games  Play with your child |
| Session 7: Providing healthy meals | Establishing eating routines  Providing healthy meals/snacks  Children’s participation in sport | Establish eating routines  Provide healthy meals and snacks  Encourage participation in sport |
| Session 8: Managing problem behaviour | Managing problems behaviours | Use planned ignoring for minor misbehaviour  Give clear calm instructions  Back up instructions with logical consequences, quiet time, or time-out |
| Session 9: Using Lifestyle Triple P strategies 1 | Implementing strategies |  |
| Session 10: Using Lifestyle Triple P strategies 2 | Implementing strategies |  |
| Session 11: Planning ahead | Family survival tips  High risk situations  Planned activities routine |  |
| Session 12: Using planned activities 1 | Implementing planned activities routine |  |
| Session 13: Using planned activities 2 | Implementing planned activities routine |  |
| Session 14: Program Close | Progress review  Maintaining changes  Problem solving for the future |  |

Forty-eight parents who are assigned to the control condition receive an intervention which consists of three components. They receive:

1) two information leaflets: one about healthy nutrition and physical activity (Netherlands Institute for Sports and Physical Activity; NISB), and one about positive parenting of the Netherlands Youth Institute (NJi) information leaflets),

2) web-based tailored feedback about providing a good parental example for your child regarding diet and physical activity (Dutch Nutrition Centre; Voedingscentrum)

3) an electronic screen time manager (Time Machine) (16). The Time Machine is an automated device that can control and monitor the use of televisions, and television-based sedentary activities.

